### Dropout criteria

Patients shall be free to withdraw their consent once given but shall not suffer any disadvantage in terms of medical practice for the withdrawal. Any participant with medical problems or unexpected serious complications occurring during treatment or follow-up period that means the study protocol cannot be completed will be analyzed on an intention-to-treat basis.

### Treatment implementation

Androgen deprivation therapy (ADT) is prescribed at the discretion of the investigator and/or physicians; administration of luteinizing hormone-releasing hormone agonists and/or anti-androgens is permitted in both treatment arms.

For RT planning, a computed tomography (CT) scan of the pelvis with a slice thickness of 2.5 mm will be obtained in all patients. Participants will be scanned in a supine position immobilized with an ankle pillow and instructed to make the bladder volume constant (empty or retain a certain amount of urine); a rectal balloon will be inserted prior to CT simulation and each treatment. There will be no routine bowel preparation. Clinical target volume (CTV) includes the prostate bed according to the Radiation Therapy Oncology Group (RTOG) contouring consensus guidelines [39]. At the discretion of the treating clinician, the pelvic lymph nodes can be included in the target volume. The planning target volume (PTV) is defined as an expansion of the CTV by 7 mm in all dimensions, other than posteriorly which will be 3–5 mm. The critical organs that are contoured include the rectum, bladder, femoral heads, penile bulb, and small bowel. The entire rectum is contoured from the anus to the rectosigmoid flexure. All patients will be treated with IMRT, and ≥ 95% of the PTV must receive the prescription dose. The use of daily image-guided techniques is strongly recommended but not mandatory.

Patients assigned to the HRT arm will receive 65 Gy of radiation in 26 fractions of 2.5 Gy (five fractions per week); for the CRT arm, 66 Gy of radiation will be administered in 33 fractions of 2 Gy (five fractions per week). The two arms differ only in the fractionation scheme. In cases of elective irradiation of the pelvic lymph nodes, 45–50 Gy will be administered using a simultaneously integrated boost technique in both arms.

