## Methods/design

### Recruitment and study design

The SHARE study is a prospective, randomized, multi-institutional trial. The protocol was approved by the institutional review boards of two participating tertiary hospitals, the Asan Medical Center and Samsung Medical Center, where it is currently ongoing. A computer-generated randomization schedule assigns the patients to either the HRT (65 Gy in 2.5-Gy fractions) or CRT (66 Gy in 2-Gy fractions) arm (Fig. 1). Random assignment is performed with a 1:1 allocation using blocked randomization, with a random block size of 4. Patients will be stratified by intermediate or high-risk according to the National Comprehensive Cancer Network (NCCN) risk classification [37] using a computer-generated random allocation sequence to ensure concealment. The clinical research nurse keeps the original random allocation sequences using the Excel file locked with a password. The process of allocation concealment from primary researchers and participants is maintained until the time of assignment. Neither the investigators nor the participants are masked to the allocated arm because blinding is not possible. For adequate participant recruitment, the investigators fully explain to potential participants the purpose, design, potential risks, and benefits of this study, as well as general ethical issues. A monthly newsletter regarding participant enrollment will be made and sent to the principal investigator and clinical research coordinators of each institution. All patients must provide written informed consent.

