### Sample size considerations and statistical analysis

The trial is powered to assess the superiority of HRT when compared with CRT. Power calculations are based on an absolute increase in bPFS of 15% (from 50 to 65%) at 5 years following HRT compared with CRT according to the dose-response relationship described by King [9]. By postulating a minimum 5-year follow-up period and allowing 5% for loss, at least 144 patients per treatment arm (288 patients in total) are required, which achieves 80% power, with a two-sided *α* of 0.05. Subgroup analyses will be performed based on the risk group (intermediate vs. high-risk group), RT field size (prostate bed only vs. elective pelvic nodal irradiation), and use of ADT.

Statistical analysis will be conducted according to the intention-to-treat approach. Survival data, PSA value, toxicity, and QoL information will be collected even though participants discontinue the planned treatment. Multiple imputation method will be used for handling missing data. The chi-square test and Student’s *t* test will be used for categorical and continuous variables of patient characteristics, respectively. Time to biochemical progression will be calculated from the end of RT. The Kaplan–Meier method will be applied to estimate bPFS curves, and the log-rank test will be used to compare the curves between the two study arms. The Kaplan-Meier method and log-rank test will be used to investigate DMFS and CSS. Acute toxicity outcomes and QoL will be estimated using the chi-square test, and late toxicity outcomes will be determined using the Kaplan-Meier method.

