As phase III trials have demonstrated the benefits of ADT in the definitive RT setting, the addition of ADT to salvage RT may be beneficial in some patients. However, the optimal timing, duration, and type of hormone treatment remain to be determined. Two phase III trials advocated the use of ADT for patients who received salvage RT. The RTOG-9601 trial, a placebo-controlled phase III study, demonstrated that the addition of 24 months’ ADT with daily bicalutamide to salvage RT resulted in significantly higher rates of overall survival (76.3 vs. 71.3% in patients receiving placebo; *P* = 0.04), and a lower incidence of metastatic prostate cancer (14.5 vs. 23%, respectively; *P* = 0.005), and death from prostate cancer (5.8 vs. 13.4%, respectively; *P* < 0.001) at 12 years [40]. Another randomized trial, GETUG-AFU 16, has also shown the superiority of adding 6 months of goserelin to salvage RT [41, 42]. After a median follow-up of 112 months, the 10-year progression-free survival was significantly better in the ADT arm versus RT alone (64 vs. 49%, respectively; *P* < 0.0001). The RADICALS trial randomly assigned patients to adjuvant RT or salvage RT, with or without ADT, and the NRG Oncology/RTOG 0534 SPPORT trial randomly assigned patients to salvage RT to the prostate bed, salvage RT to the prostate bed with ADT, or salvage RT to the prostate bed and the pelvic lymph nodes with ADT. The results of these trials could provide further evidences concerning the administration of postoperative ADT. To date, it is uncertain whether ADT in combination with salvage HRT improves biochemical control. In the trial outlined here, the authors will conduct subgroup analyses according to the use of ADT and examine the benefit derived from combined therapy. We anticipate that HRT will demonstrate favorable biochemical control and acceptable toxicity in prostate cancer patients with biochemical recurrence after radical prostatectomy. If HRT is seen to be superior to CRT, it will indicate the benefit of escalating dose delivery to the prostate bed, which will also improve patients’ convenience and reduce healthcare costs.

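### ADT and pelvic-node choices need not be fixed before the arm is known, yet they define subgroups, and the planned look at ADT benefit is a non-randomised comparison

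*Protocol article*

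**What the plan says.** Under Treatment implementation, the protocol article says "Androgen deprivation therapy (ADT) is prescribed at the discretion of the investigator and/or physicians", with the same permission in both arms. For the field it says "At the discretion of the treating clinician, the pelvic lymph nodes can be included in the target volume". The same section asserts that fractionation is the only respect in which the arms differ.

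Under Recruitment and study design: "Neither the investigators nor the participants are masked to the allocated arm because blinding is not possible". On allocation: "Random assignment is performed with a 1:1 allocation using blocked randomization, with a random block size of 4". The only stratification factor given is risk group: "Patients will be stratified by intermediate or high-risk according to the National Comprehensive Cancer Network (NCCN) risk classification".

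The primary endpoint, bPFS, counts a detectable PSA after salvage RT as an event. The arms are compared by log-rank test on an intention-to-treat basis. Besides risk group, the subgroup factors are "RT field size (prostate bed only vs. elective pelvic nodal irradiation), and use of ADT". The Discussion adds that the authors will "conduct subgroup analyses according to the use of ADT and examine the benefit derived from combined therapy", and it would read superiority of HRT as showing a benefit of dose escalation to the prostate bed.

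**The concern.** Two co-treatments that may affect the primary outcome are discretionary, and the people choosing them can know the arm. The article's own Discussion cites a randomised trial in which ADT added to salvage RT gave 10-year progression-free survival of 64% against 49%. Three things are at stake.

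- **Subgroups.** A subgroup formed by actual use is protected by randomisation only if use cannot respond to the arm. The article does not secure that.
- **Attribution.** If co-treatment differs by arm, a difference in bPFS is no longer a difference due to fractionation alone, which is how the article proposes to read it.
- **ADT benefit.** ADT is not randomised. Men who receive it will differ from men who do not, so setting the two groups side by side inside this trial is confounded by indication even if ADT use is identical in the arms.

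**Working it through.** **1. The plan's own figure.** Inputs from Sample size considerations: 5-year bPFS 50% vs 65%, two-sided alpha 0.05, power 80%, minimum follow-up 5 years, 5% loss.

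- Hazard ratio under proportional hazards: ln(0.65)/ln(0.50) = 0.621, log HR = −0.476.
- Events (Schoenfeld): 4 × (1.96 + 0.842)² / 0.476² ≈ 139.
- With exponential survival and uniform accrual over 31 months (August 2019 to March 2022), the mean event probability is 0.4985. So 139/0.4985 gives 279 patients, and 279/0.95 gives 294. With 3 years' accrual the probability is 0.509, giving 274 and then 289.

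The stated 288 is reproduced within about 2%. The sample size is not in dispute; 139 events is the working figure below.

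**2. Effect of an ADT imbalance on the primary test.** Assumptions not in the documents: ADT use of 30 to 50% in the reference arm, a 10- or 20-point difference between arms, and an ADT hazard ratio obtained by converting the cited 64% vs 49%: ln(0.64)/ln(0.49) = 0.626. That conversion carries a 10-year contrast from one ADT regimen over to 5-year bPFS.

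With ADT use u, 5-year bPFS is (1 − u)·e^(−5λ) + u·e^(−5λ × 0.626). Setting this to 0.50 at u = 0.40 gives λ = 0.166 per year, with bPFS 0.4365 without ADT and 0.5953 with it. Then, with no effect of fractionation:

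| ADT use in other arm | bPFS | Apparent HR | Shift in log HR |
|---|---|---|---|
| 50% | 0.5 × 0.4365 + 0.5 × 0.5953 = 0.516 | ln(0.516)/ln(0.50) ≈ 0.955 | 0.046 |
| 60% | 0.4 × 0.4365 + 0.6 × 0.5953 = 0.532 | ≈ 0.911 | 0.093 |

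Reference use of 30% or 50% changes these very little.

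SE(log HR) = 2/√139 = 0.170.

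- **More ADT in CRT, planned effect true.** Power = Φ((0.476 − 0.046)/0.170 − 1.96) ≈ 72% for 10 points, and Φ((0.476 − 0.093)/0.170 − 1.96) ≈ 62% for 20 points.
- **More ADT in HRT, no true effect.** Two-sided rejection = Φ(−1.96 + 0.046/0.170) + Φ(−1.96 − 0.046/0.170) ≈ 5.9%; with 0.093 it is about 8.5%.
- **More ADT in CRT, no true effect.** Two-sided rejection is much the same, but the excess is false wins for CRT. The chance of falsely declaring HRT superior falls from 2.5% to Φ(−1.96 − 0.046/0.170) ≈ 1.3%, or about 0.6% for 20 points.

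**Range.** A simulation of 144 per arm with an unadjusted log-rank test, assumed ADT hazard ratios of 0.5 to 0.6 and ADT use around 40%, gave two-sided type I error of about 6.3 to 7.1% (10 points) and 10 to 14% (20 points). Power with more ADT in CRT was about 65 to 72% and 50 to 61%.

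The documents give no figure from which the effect of the nodal field could be sized, so none is offered.

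**3. The ADT subgroups.** With 139 events split evenly, the standard error of a treatment-by-ADT interaction is √(16/139) = 0.339. An interaction test has 80% power only for a ratio of hazard ratios of about exp(2.8 × 0.339) = 2.6. These subgroups can be descriptive at best.

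**4. The ADT comparison.** No arithmetic is needed. ADT is discretionary under Treatment implementation, and the Discussion plans to examine its benefit by subgroup. Balance between HRT and CRT does not make men with and without ADT comparable.

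**The case against.** The strongest reply is that much of this is inferred from silence. The article does not say when ADT or the field is chosen, and a condensed article may omit a rule that the full protocol contains. Nothing in it suggests that prescribing depends on the arm. If ADT follows prognosis, randomisation balances it in expectation. Leaving co-treatment to usual practice is a legitimate pragmatic design, an unadjusted log-rank test is a legitimate primary analysis, and not stratifying by ADT or field is a preference rather than an error.

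Most of that stands, and it rules out several readings that a reader might reach:

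- That the subgroups are in fact formed after randomisation. The documents support only that they may be.
- That the primary test is invalid. Intention-to-treat still compares HRT and CRT, each with whatever co-treatment follows.
- That clinicians compensating the CRT arm would manufacture a win for HRT. Compensation works against HRT: it costs power and lowers the chance of a false HRT win. Direction cannot be known from the documents.
- That the trial will claim an ADT benefit. The Discussion says only that it will be examined, and ADT is no endpoint.

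The reply does not cover three things the article does state: subgroups defined by use rather than intent, the unqualified assertion that the arms are otherwise alike, and the aim of examining ADT benefit. A later analysis plan also cannot recover intent that was never recorded.

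**Conclusion.** The point holds in a limited form. The ADT comparison is confounded by indication without any assumption about clinician behaviour. The ADT and field subgroups may depend on allocation because the article does not require the choices to precede it. The primary comparison stands as a comparison of policies; reading it as an effect of fractionation or dose depends on balanced co-treatment.

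The possible size is modest for a 10-point imbalance and material for 20 points: power of about 72% or 62% if CRT receives more ADT, and two-sided type I error of about 5.9% or 8.5% if HRT does. These figures rest on the assumed ADT use, imbalance and hazard ratio and show what could happen; they do not forecast it. This is worth correcting, but it does not undermine the trial or its sample size.

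**What to change.** None of this changes who receives ADT or nodal RT.

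1. For any patients still to be randomised, record intended ADT (yes/no) and intended field before the arm is released. For those already enrolled, use intent documented before randomisation where it exists.
2. Define the ADT and field subgroups by that intent, with a treatment-by-factor interaction test. Where no intent is documented, label use-based subgroups as post-allocation and exploratory.
3. Keep the log-rank test as primary. Add a pre-specified supporting Cox model adjusted for intent and NCCN risk, and report actual ADT and field use by arm.
4. Label any ADT versus no-ADT comparison as non-randomised and exploratory, and qualify the statement under Treatment implementation that only fractionation differs.

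**Cost.** Two form fields, some retrospective data work and revised wording. The form change would reach few patients: at publication in October 2021 about 26 of the 31 planned recruitment months had passed. Intent data for earlier patients will be incomplete, and the trial gives up a stronger statement about ADT.

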### Data collection and follow-up period

Patient data will be collected according to the schedule shown in Fig. 2, i.e., prior to initiating RT, weekly during RT, every 3 months for the first 2 years after RT, every 6 months for years 3–5, and then annually thereafter. The following patient data will be recorded in case report forms: urologic/gastrointestinal (GI) toxicities using the Common Toxicity Criteria for Adverse Events (CTCAE v5.0), patient-reported outcomes, QoL, and PSA levels. A pop-up sticker note will be generated automatically on the electronic medical record system to improve adherence to intervention protocols and follow-up laboratory tests. These outcome data will be aggregated as median and interquartile range. If tumor recurrence or metastases are suspected, pelvic magnetic resonance imaging, CT, and/or bone scans can be performed at the discretion of the investigator.

**Fig. 2 Fig2:**
[figure not shown]
Intervention and assessment schedule for the trial according to the Recommendations for Interventional Trials (SPIRIT). PRO, patient-reported outcomes; QoL, quality of life; PSA, prostate-specific antigen

To ensure patient data protection, separate identification codes will be given to all patients. Data will password-protected and only accessible by investigators. All data will be deleted 3 years after the end of the study.

### Assessment of primary and secondary endpoints

The primary endpoint is to investigate whether HRT improves 5-year bPFS versus CRT in patients with biochemical recurrence after radical prostatectomy. Biochemical progression-free survival is counted from the date of the salvage radiotherapy to biochemical progression, clinical progression, or death of any cause. Biochemical progression after RT is defined as detectable PSA after salvage RT. Secondary endpoints are to compare acute and late toxicities based on CTCAE v5.0 and QoL and to determine 5-year distant metastasis-free survival (DMFS) and cancer-specific survival (CSS).

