### Inclusion criteria

Eligible patients are required to have a diagnosis of histologically confirmed prostate adenocarcinoma after radical prostatectomy and must fulfill the following criteria: aged ≥ 19 years, an Eastern Cooperative Oncology Group performance status 0–1, intermediate or high risk according to the NCCN guidelines [37], and total serum PSA level after prostatectomy > 0.2 and ≤ 1.0 ng/ml. Patients should also have adequate bone marrow (absolute neutrophil count ≥ 1500 cells/mm^3^; hemoglobin concentration ≥ 8.0 g/dl; platelet count ≥ 50,000 cells/mm^3^), liver (total bilirubin < 1.5 times the maximum normal value; alanine aminotransferase or aspartate aminotransferase < 2.5 times the maximum normal value), and renal (creatinine < 2.0 ng/dl) function, as assessed by tests performed within the 6-month period prior to enrollment.

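### The primary event counts any measurable PSA after radiotherapy, although every patient starts with one, so a falling PSA can be scored as progression

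*Protocol article*

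**What the plan says.** Under Assessment of primary and secondary endpoints, the primary endpoint is 5-year biochemical progression-free survival (bPFS), "counted from the date of the salvage radiotherapy to biochemical progression, clinical progression, or death of any cause". The biochemical component is then defined: "Biochemical progression after RT is defined as detectable PSA after salvage RT". Nothing elsewhere in the article qualifies that sentence.

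Three other places bear on it:

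- Inclusion criteria: patients must have a "total serum PSA level after prostatectomy > 0.2 and ≤ 1.0 ng/ml".
- Data collection and follow-up period: assessments, including PSA, are made "every 3 months for the first 2 years after RT, every 6 months for years 3–5, and then annually thereafter".
- Sample size considerations and statistical analysis: power rests on an "absolute increase in bPFS of 15% (from 50 to 65%) at 5 years following HRT compared with CRT", and the arms are compared by log-rank test.

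**The concern.** A rule that calls any measurable value a failure makes sense only where the marker was unmeasurable beforehand. Here the entry criterion guarantees the opposite. PSA has to fall through the measurable range before it can disappear, and the rule does not wait for that or ask which way PSA is moving. As an illustration, a patient who goes from 0.6 to 0.1 ng/ml at the first post-radiotherapy visit has responded, yet has the primary event if the assay registers 0.1.

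Such events would collect at the first visit. If they arise equally in both arms and are unrelated to who truly relapses, they add noise and reduce the difference that the trial is powered to find. If they arise unequally, they bias the comparison. The sentence decides who has the primary event, so the main result depends on it.

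**Working it through.** **Inputs from the article.** 5-year bPFS 50% (conventional) and 65% (hypofractionated); 144 per arm; 5% loss; two-sided α 0.05; 80% power; minimum follow-up 5 years; recruitment August 2019 to March 2022, about 2.6 years; the visit schedule quoted above. Evaluable patients: 144 × 0.95 = 136.8, taken as 137 per arm.

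**Step 1: the plan's own sample size.** Under proportional hazards, HR = ln 0.65 / ln 0.50 = 0.621. Schoenfeld events = 4 × (1.960 + 0.842)² / (ln 0.621)² ≈ 139. With exponential survival, uniform accrual over 2.6 years and at least 5 years of follow-up, the mean event probability is 0.498. That gives 139 / (2 × 0.498), or 140 per arm, and 140 / 0.95, or 148 with loss. With 3 years of accrual the figures are 137 and 145. The stated 144 is within 3% of these, and 137 evaluable per arm gives 79–80% power. The sample size is not the fault, but it has no slack.

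**Step 2: the rule against the entry criterion.** Measurable at entry: all patients, since all exceed 0.2 ng/ml. Condition for the event: measurable at any time after radiotherapy. Earliest scheduled look: three months after radiotherapy. Nothing separates a value on its way down from one on its way up.

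**Step 3: effect on the 5-year rates.** Let f be the share of each arm flagged at the first visit only because PSA is still measurable. The article gives no value for f, so it is varied. If f is equal in both arms and independent of true outcome, each rate becomes p × (1 − f). At f = 20%: 0.50 × 0.80 = 0.40 and 0.65 × 0.80 = 0.52, a difference of 12 points instead of 15. At f = 10% the difference is 13.5 points, and at 30% it is 10.5.

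**Step 4: effect on power.** Log-rank simulation with 137 per arm, exponential event times, events detected on the stated visit grid and censoring at the last visit:

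| f in each arm | Flags independent of outcome | Flags only in patients who would fail within 5 years |
|---|---|---|
| 0% | about 77% | about 77% |
| 10% | about 64% | about 69–77% |
| 20% | about 54% | about 69–77% |
| 30% | about 43% | about 69–77% |

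Repeated runs of the independent case agree to within about 3 points. With continuous event times instead of visits, the independent case gives 80%, 67%, 55% and 46%. The baseline is higher because follow-up is not cut back to the last visit, but the loss is of similar size. In the right-hand column the 5-year difference stays at 15 points, because every flagged patient would have been counted by year 5 anyway; only the timing moves.

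**Step 5: unequal f.** The courses differ by 33 − 26 = 7 fractions, which at five per week is 1.4 weeks. Visits are timed from radiotherapy, so conventional-arm patients are further from their first fraction when first tested. Equal f is therefore not guaranteed. With f = 25% in the hypofractionated arm and 20% in the other, the rates are 0.65 × 0.75 = 0.4875 and 0.50 × 0.80 = 0.40, a difference of 8.75 points, and simulated power is near 30%. Reversed, they are 0.52 and 0.375, a difference of 14.5 points, and power is above 70%. The direction cannot be determined from the article.

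**The case against.** The strongest reply is that the power loss depends on two things the article does not supply. One is f itself, which turns on PSA kinetics and the assay limit. The other is whether early flags are unrelated to outcome. A PSA still measurable after radiotherapy may well mark patients who will relapse; if so, little power is lost. Both points stand, and the loss is therefore a range whose lower end is close to nothing.

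It can also be said that this is a condensed article and the full protocol may carry a numeric limit. That may be so. But the article does not leave the definition out; it states one as a complete sentence, and that sentence does not work in a population measurable at entry. If a threshold was intended, the published wording still needs correcting.

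A reader might infer more than the document supports:

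- *That the 50% and 65% planning rates are invalid, or that results cannot be compared with the bPFS figures cited.* Both need the failure definitions used in the cited work, which the article does not give.
- *That the two hospitals' assays differ.* Nothing is said about the assays.
- *That discretionary hormone therapy makes this rule measure hormone use.* PSA suppression would affect a nadir-based rule too, so it is not a fault of this definition in particular.
- *That the entry criterion supplies a ready-made rise threshold.* It is an absolute level above 0.2 ng/ml, not a rise above nadir.

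**Conclusion.** The definition is wrong as written and should be changed. That conclusion needs only the event sentence, the entry criterion and the visit schedule.

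The size of the harm is conditional. If f is equal by arm and independent of outcome, power goes from about 77% to about 64%, 54% and 43% at f = 10%, 20% and 30%. If the flagged patients would have failed anyway, it remains about 69–77%. If f differs between arms, the result is bias of unknown direction. It would be too strong to say that many recorded events will not be progression, because the document gives no basis for a value of f.

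**What to change.** Amend the analysis definition of the primary event so that a falling PSA is not an event:

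- Require a rise after radiotherapy: above the post-radiotherapy nadir, or a continued rise in patients whose PSA never falls.
- Judge it against one numeric threshold, pre-specified by the sponsor and common to both hospitals.
- Require confirmation by a second consecutive value, and date the event at the first.
- Keep the present any-measurable-value rule as a sensitivity analysis.
- Check that the 50% and 65% planning rates suit the amended definition.

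No new data collection is needed, since PSA is already recorded at the scheduled visits. The costs are that events are declared slightly later because of confirmation, and that this is a primary-endpoint amendment in an open-label trial that began recruiting in August 2019. It must therefore be documented and made without reference to outcome data by arm.
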